## Abstract

**Background:**

The Finnish Geriatric Intervention Study to Prevent Cognitive Impairment and Disability (FINGER) was the first to show that multidomain lifestyle interventions can enhance brain health and reduce cognitive decline. However, the clinical effectiveness and delivery of the FINGER model within primary care settings remain unexplored. This paper presents the protocol for the STRONGER 60+trial, which aims to evaluate both the clinical effectiveness and real-world delivery of an adapted FINGER-based intervention in primary care.

**Methods and analysis:**

This 6-month randomised controlled clinical effectiveness trial will be conducted in primary care and will include adults aged 60 and older with vascular or lifestyle-related risk factors for dementia. A total of 80 participants will be randomised to either a structured, supervised multidomain lifestyle intervention or a self-guided version of the same programme. The intervention includes nutritional guidance, physical exercise, cognitive training, social engagement and management of vascular and metabolic risk factors. Data will be collected at baseline, 6 months (primary endpoint) and 12 months post-randomisation. The primary outcome is the change in a composite healthy lifestyle score at 6 months. In addition, the study will explore delivery processes and stakeholder (participant and healthcare professional) perspectives using both qualitative and quantitative methods.

**Ethics and dissemination:**

The study has been approved by the Swedish Ethical Review Authority (approval numbers: 2020–05785, 2021–06413-02, 2022–05454-02) and will follow the principles of the Declaration of Helsinki. Ethical procedures for informed consent, confidentiality and data management will be strictly observed. Results will be disseminated through scientific publications, conferences and targeted outreach to healthcare professionals and the general public.

**Trial registration number:**

NCT07117916.

STRENGTHS AND LIMITATIONS OF THIS STUDYRandomised controlled design with blinded outcome assessment strengthens validity.Builds on pilot testing with a refined intervention and validated assessment battery feasible for primary care.Intervention delivery is systematically evaluated through predefined recruitment, retention and adherence metrics.Qualitative methods provide insights into barriers and facilitators of implementation in primary care.A single-country setting may limit generalisability.

## Introduction

 Dementia currently affects an estimated 57 million people worldwide, a number projected to rise to 153 million by 2050. It is the seventh leading cause of death globally and a major contributor to disability and dependency among older adults.^1^ With limited progress in developing accessible, disease-modifying treatments,^2 3^ dementia prevention has become a public health priority.^4^ Nearly half of all dementia cases may be preventable by addressing modifiable risk factors such as unhealthy diet, physical and cognitive inactivity, social isolation and vascular conditions like hypertension.^4 5^

Given the multifactorial nature of dementia, multidomain lifestyle interventions targeting several risk factors simultaneously show the most promise. The Finnish Geriatric Intervention Study to Prevent Cognitive Impairment and Disability (FINGER) was the first randomised controlled trial to demonstrate that such interventions can enhance cognitive function and promote brain health.^6^ The study involved 1260 individuals aged 60–77 at increased risk of dementia, who received a 2-year intervention combining nutritional guidance, physical exercise, cognitive training, social activities and cardiovascular monitoring. The control group received standard health advice. Beyond cognitive improvements, the FINGER trial also reported gains in physical function, quality of life and reduced multimorbidity.^7^,^9^ These findings have been supported by other international trials through the World-Wide FINGERS (WW-FINGERS) network, a global initiative spanning over 70 countries focused on lifestyle-based dementia prevention.^10^

For an intervention to be truly evidence-based, it must demonstrate effectiveness not only in controlled research environments but also in real-world clinical settings.^11^ However, many promising interventions fail to translate into practice due to a lack of contextual adaptation.^11^ Clinical effectiveness research addresses this gap by evaluating outcomes in routine care settings, using diverse populations and emphasising external validity.^12^ It also considers the interaction between the intervention and the healthcare context—examining feasibility, acceptability and transferability.

A structured approach to testing interventions in clinical settings can reveal practical challenges and success factors. Understanding the perspectives of both patients and healthcare providers is essential for developing interventions that are not only effective but also feasible and sustainable in everyday practice.^12 13^ Exploring aspects such as recruitment, retention and adherence provides insights into what supports or hinders successful delivery, helping optimise interventions for different populations and healthcare systems.^13^

Recognising the need for context-specific strategies, the WHO recommends adapting dementia prevention efforts to local healthcare systems, with an emphasis on primary care.^4^ The FINGER model has been adapted and tested in other populations, including individuals with prodromal Alzheimer’s disease in the MIND-ADmini trial. That study demonstrated high feasibility and adherence, and participants receiving both the lifestyle intervention and medical food showed improvements in overall lifestyle, cognitive function and daily functioning after 6 months.^14^ However, the clinical effectiveness and delivery of the FINGER model have not yet been studied in a primary care setting.

The STRONGER 60+trial aims to fill this gap by evaluating the clinical effectiveness and delivery of an adapted FINGER-based multidomain lifestyle intervention in primary care. It also seeks to explore the perspectives of healthcare professionals and participants on the intervention and its delivery. This paper presents the study protocol for the STRONGER 60+trial.

## Methods and analysis

### Trial design and participants

The STRONGER 60+trial is a 6-month randomised controlled clinical effectiveness study conducted in primary care settings in Sweden. The trial follows the Consolidated Standards of Reporting Trials (CONSORT) guidelines^15^ and is registered at ClinicalTrials.gov (ID: NCT07117916). This protocol is also reported in accordance with the SPIRIT (Standard Protocol Items: Recommendations for Interventional Trials) guidelines.^16^

Recruitment will take place through advertisements posted at participating primary care clinics and on their public websites. Individuals aged 60 and older who express interest in the study will be pre-screened by the research team using the CAIDE (Cardiovascular Risk Factors, Ageing and Dementia) Risk Score.^6^ Those scoring ≥6—indicating elevated dementia risk—will be invited for an in-person screening visit to confirm eligibility. The CAIDE score (range: 4–15) is based on age, sex, education, systolic blood pressure, body mass index (BMI), total cholesterol and physical activity.^17^ Additional inclusion criteria are a Mini-Mental State Examination (MMSE) score of ≥24,^18^ and ability to walk independently indoors and outdoors (with or without a mobility aid). Exclusion criteria include diagnosed dementia and residence in a nursing home.

Eligible individuals will provide written informed consent and complete baseline assessments at one of the participating primary care units. Participants will be informed about the random assignment process and the nature of the two study arms—one involving structured, in-person sessions and the other a self-guided version of the same intervention. They will also be advised that one approach may be more effective than the other.

Participants will be randomly allocated (1:1) to either: (1) an intervention group: receiving a structured multidomain lifestyle programme (including nutritional guidance, physical exercise, cognitive training, social engagement and vascular risk management), or a control group: receiving a self-guided version of the intervention. Randomisation will be computer-generated using block randomisation. Outcome assessors will be blinded to group allocation, and participants will be instructed not to disclose their assignment to evaluators. The study design is outlined in figure 1.

**Figure 1 F1:**
[figure not shown]
Design of the STRONGER 60+trial.

An initial pilot phase (March 2022 to June 2024) helped refine procedures and confirmed that the intervention was feasible, safe and well-accepted by participants (results in preparation). The trial experienced some delays due to the COVID-19 pandemic but resumed with full protocol adjustments thereafter.

### Intervention programme

#### The self-guided intervention (control group)

Participants in the control group will receive a self-guided version of the intervention. All participants, regardless of group allocation, will meet with the study nurse at screening, baseline and 6 months post-randomisation for health assessments. These assessments will include blood sampling, blood pressure, weight, BMI and hip and waist circumference. A medical history and physical examination will be performed by the study nurse or physician. At the baseline visit, all participants will receive both verbal and written guidance from the study nurse on maintaining a healthy diet, staying physically, cognitively and socially active, and managing vascular risk factors. This information, aligned with national and international guidelines (eg, on nutrition and physical activity), mirrors the content provided to the intervention group and is intended to support vascular risk reduction and promote healthy ageing. Participants will have access to the study team throughout the trial and may contact them with questions or concerns. If needed, referrals to appropriate medical care will be provided.

#### The structured multidomain lifestyle intervention (intervention group)

In addition to health advice, participants in the intervention group will receive a structured, multimodal lifestyle programme comprising nutritional guidance, physical exercise, cognitive training and social engagement and monitoring and management of vascular and metabolic risk factors. The STRONGER 60+intervention is based on the FINGER protocol^6^ and has been specifically adapted for primary care to enhance feasibility and scalability. Key adaptations include (1) delivering physical exercise sessions at external gym facilities rather than at primary care centres, and (2) shortening the intervention duration from 2 years to 6 months.

#### Nutritional guidance

The nutritional component of the intervention consists of one group session lasting approximately 60–75 min and two individual counselling sessions of about 30 min each with the study dietician. During the individual sessions, the participant’s dietary habits will be thoroughly assessed to provide tailored advice on improving nutritional intake and incorporating healthy changes into daily routines. The group session will offer additional information and motivation through practical, educational activities aimed at supporting long-term lifestyle changes. Participants will also receive written materials, including tips on healthy food choices and recipes. To improve accessibility, and based on pilot phase feedback, scheduling with the dietician will be made more flexible to allow participants to begin this part of the intervention earlier.

The nutritional guidance follows the Nordic Nutrition Recommendations 2023, as adapted for Swedish conditions by the Swedish National Food Agency.^19^ In addition to general dietary recommendations, special focus will be placed on nutrition known to support brain health and reduce dementia risk.^6^ This includes a high intake of fruits and vegetables, whole grain cereals and low-fat dairy and meat products, while limiting the consumption of sugar and salt. Participants will be encouraged to use vegetable margarine and rapeseed oil in place of butter, and to eat fish at least two times per week.

#### Physical exercise

The physical exercise component is based on international guidelines^20^ and adapted from the FINGER exercise programme^6^ to suit primary care settings. To support participant adherence, the programme begins with a group session led by a physiotherapist, introducing participants to a self-monitored exercise routine designed to be performed at an external gym.

Participants will be encouraged to attend gym sessions two to three times per week, incorporating both strength training and aerobic exercise in accordance with current guidelines for older adults. In addition, they will be advised to regularly include balance and flexibility exercises as part of their weekly routine, promoting physical function and fall prevention.^20^ Findings from the pilot phase highlighted the importance of accessibility and social interaction for sustained motivation. Therefore, gym facilities should be conveniently located and provide supervised group classes to promote both safe exercise and social engagement.

#### Cognitive training and social activities

Cognitive training involves both a group session and individual, home-based sessions. The group session, led by a healthcare professional (eg, occupational therapist or nurse), lasts approximately 45 min and provides an overview of neurocognitive disorders along with coping and reasoning strategies. Based on pilot feedback, this session also introduces the digital training platform, helps participants adapt it to their preferred device (tablet, computer or smartphone) and offers time for questions.

Individual training consists of computer-based exercises performed at home at least two times per week, each session lasting 15–20 min. The programme includes eight tasks targeting executive function (eg, updating and mental set shifting), working memory (spatial maintenance), episodic memory (relational and spatial tasks) and mental speed (odd-even and high-low number tasks). As in the FINGER trial, task difficulty automatically adjusts based on individual performance.^6^

Social interaction is actively encouraged throughout the programme, particularly during gym and group activities, due to its known benefits for brain health. Participants also receive guidance on engaging in mentally stimulating and socially enriching activities, such as learning new skills, pursuing hobbies, playing music, studying languages, reading, gaming and adopting techniques to manage stress and improve sleep.

#### Monitoring and management of vascular and metabolic risk factors

Management follows established evidence-based guidelines^21^ and includes a follow-up appointment with clinical staff at 3 months. During this visit, key health indicators—such as blood biomarkers (lipids, glucose), blood pressure, weight, BMI and hip and waist circumference—will be measured. Participants will receive tailored lifestyle recommendations based on these assessments. Those with abnormal or untreated results will be referred to their regular general practitioner for further evaluation and care. Additionally, smokers will be offered cessation support, and participants will be encouraged to have their vision, hearing and oral health checked as needed.

### Outcome assessments

Data will be collected at baseline, and at 6 and 12 months post-randomisation, for all participants—regardless of group assignment—at a participating primary care centre (see table 1). The primary outcome is the clinical effectiveness of the intervention at 6 months, measured by changes in a composite healthy lifestyle score. Outcomes at 12 months will be assessed to evaluate the sustainability of any observed effects over time.

**Table 1 T1:** Assessment timeline for trial variables

	Time point		
Assessment	Baseline	6 months post-randomisation	12 months post-randomisation
Primary outcome			
Composite healthy lifestyle score	X	X	X
Dietary intake: diet questionnaire	X	X	X
Physical activity: ActiGraph	X	X	X
Cognitive and social activities: Self-reported participation	X	X	X
Vascular and metabolic risk factors: BMI, hip-waist ratio, blood pressure, cholesterol and glucose levels and smoking	X	X	X
Secondary outcomes			
Physical function: 10-metre walking test and SPPB	X	X	X
Cognitive function: MMSE	X	X	X
Depressive symptoms: Geriatric Depression Scale	X	X	X
Health-related quality of life: RAND-36 Health Survey	X	X	X
Sleep quality: PSQI	X	X	X
Additional data			
Age, sex and education	X		
Employment and cohabitation status	X	X	X
CAIDE risk score	X		
Diseases and prescribed drugs	X	X	X

.BMI, body mass index; CAIDE, Cardiovascular Risk Factors, Ageing and Dementia Risk Score; MMSE, Mini-Mental State Examination; PSQI, Pittsburgh Sleep Quality Index; SPPB, Short Physical Performance Battery.

#### Primary outcome

The primary outcome is change in a composite healthy lifestyle score originally developed and used in the FINGER studies.^22^ The score comprises four domains: dietary intake, physical activity, cognitive and social engagement (combined) and cardiovascular risk burden. Each domain is first quantified using its respective assessment method (described below). For scoring, domain-specific values are divided into tertiles, with 0 points assigned to the least favourable tertile, 1 point to the intermediate tertile and 2 points to the most favourable tertile. The total composite score is calculated as the sum of the four domain scores and ranges from 0 to 8, with higher values indicating a healthier overall lifestyle. Change in this composite score between assessments reflects each participant’s change in adherence to a healthy lifestyle across the four domains. Assessments are conducted at baseline, 6 months (primary endpoint) and 12 months post-randomisation.

Dietary intake will be assessed using a food frequency questionnaire incorporating the Mediterranean Diet Adherence Screener and the Healthy Diet Index.^23^ Physical activity will be measured objectively using the ActiGraph GT3X accelerometer (ActiGraph, Pensacola, Florida, USA), quantified as the average percentage of daily time spent in moderate-to-vigorous physical activity over 1 week.^24^ Cognitive and social engagement will be evaluated through self-reported participation in cognitively stimulating (eg, studying, writing, puzzles, crafts, courses) and social activities (eg, volunteering, clubs, caregiving, card/board games).^25^ Vascular and metabolic risk burden will be assessed through changes in BMI, waist-to-hip ratio, blood pressure, lipid and glucose levels and smoking status.

#### Secondary outcomes

Secondary outcomes will be assessed at baseline, 6 months and 12 months post-randomisation, focusing on changes in physical and cognitive function, depressive symptoms, health-related quality of life and sleep quality. Physical function will be measured using the 10-metre walking test^26^ and the Short Physical Performance Battery.^27^ Cognitive function will be assessed with the MMSE.^18^ Depressive symptoms will be evaluated using the Geriatric Depression Scale,^28^ while health-related quality of life will be measured with the RAND-36 Health Survey.^29^ Sleep quality will be assessed using the Pittsburgh Sleep Quality Index.^30^ Demographic data will include age, sex, educational level, employment status and cohabitation status. The CAIDE dementia risk score^6^ will also be calculated. Information on chronic diseases and prescribed medications will be extracted from patient medical records.

### Assessing stakeholder perspectives and delivery of the intervention

Stakeholder perspectives will be explored through in-depth individual interviews with participants and focus group discussions with healthcare professionals involved in delivering the intervention. Participant interviews will focus on overall satisfaction and perceptions of the programme’s strengths and limitations.^31^ Interviews with healthcare professionals will focus on identifying perceived barriers and facilitators to implementing the intervention in primary care settings. The findings will be discussed in relation to the Consolidated Framework for Implementation Research.^31 32^ Purposive sampling will be used to ensure a diverse sample of interviewees based on characteristics such as age and sex. The number of interviews will be determined by the richness and depth of the data collected.

The delivery of the STRONGER 60+intervention will be assessed through analysis of recruitment, retention and adherence rates among participants in the intervention group. Recruitment rate is defined as the proportion of eligible individuals who consent to participate after being invited, with ≥50% considered successful.^33^ Retention rate refers to the proportion completing the 6-month intervention, with a dropout rate below 35% indicating acceptable retention. Reasons for dropout and occurrence of any adverse events will be recorded as reported by participants.^33^ Overall adherence will be calculated as the proportion of attended sessions relative to the total number offered.^14^ Adherence will also be assessed within each domain of the intervention:

Nutritional guidance: Defined as attendance at both the group and individual sessions.Physical exercise: Based on gym attendance logs.Cognitive training: Measured by participation in group sessions and frequency of use of the digital training platform, as recorded by the system.Vascular and metabolic risk management: Defined as attendance at the 3-month follow-up visit for cardiovascular assessments with clinical staff.^14^

### Data analysis

#### Statistical analysis

This study focuses on clinical effectiveness and intervention delivery; therefore, a formal sample size calculation was not conducted. However, based on comparable studies,^14 33^ a target sample size of 80 participants (40 per group) is deemed sufficient to meet the study objectives.

Differences in adherence to healthy lifestyle changes—both overall and within individual domains—from baseline to 6 and 12 months will be analysed using linear mixed-effects models. These models will include an interaction term between group (structured multidomain lifestyle intervention vs self-guided intervention) and time to evaluate differential changes over time. In line with the FINGER study, analyses will be conducted on a modified intention-to-treat population, defined as all randomised participants with at least one post-baseline measurement. Recruitment rates, retention rates and adherence (overall and by domain) will be reported using descriptive statistics.

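### The primary mixed model states no baseline adjustment and, as ordinarily fitted, estimates the 6-month effect less precisely than the baseline data allow

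*Protocol article*

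**What the plan says.** The Primary outcome section defines the endpoint as a change: "The primary outcome is change in a composite healthy lifestyle score originally developed and used in the FINGER studies". On its scale it says: "The total composite score is calculated as the sum of the four domain scores and ranges from 0 to 8". Assessments are at baseline, 6 months (primary) and 12 months.

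The Statistical analysis section says that differences "from baseline to 6 and 12 months will be analysed using linear mixed-effects models", with an "interaction term between group (structured multidomain lifestyle intervention vs self-guided intervention) and time to evaluate differential changes over time". The same models serve the composite and the single domains. The section does not say whether baseline is an outcome visit with free arm means, an outcome visit with a common mean, or a covariate. The analysis set is everyone randomised who has at least one measurement after baseline.

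On size, the same section states that "a formal sample size calculation was not conducted" and that "a target sample size of 80 participants (40 per group) is deemed sufficient to meet the study objectives". Under Trial design and participants, allocation is 1:1.

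**The concern.** The plain reading of a group-by-time model running from baseline onwards treats baseline as one of the outcome visits and lets the arms have different baseline means. The model then spends information estimating a baseline difference that randomisation already makes zero in expectation, and subtracts that noisy estimate from the 6-month difference. The cost is a larger standard error for the primary contrast.

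This matters more here than in a large trial. The number of participants is set without a power calculation. The comparator is a self-guided version of the same programme, so the contrast may be modest. Baseline is collected on everyone in any case.

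**Working it through.** **Inputs.** From the article: 40 per arm, 1:1 allocation, a 0 to 8 score made of four tertile scores, visits at baseline, 6 and 12 months. Assumed, because the article gives none: the baseline-to-6-month correlation rho (0.3 to 0.8), equal variance at both visits, and, for power only, a two-sided 5% test and a true difference of 0.5 baseline SD. The target of 80 cannot be reproduced, since no effect size, SD, significance level or power is given.

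**Formulas** (score variance set to 1, complete data):
- Free arm means at baseline: the 6-month interaction is the difference in mean change. Variance per participant = 2(1 − rho).
- Baseline-adjusted, or common baseline mean: variance per participant = 1 − rho².
- Ratio, adjusted to unadjusted = (1 − rho²) / [2(1 − rho)] = (1 + rho)/2.
- Standard error of the contrast = √(variance × 2/40).

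At rho 0.5: unadjusted √(1.00 × 2/40) = 0.224; adjusted √(0.75 × 2/40) = 0.194; ratio of variances 0.75.

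| rho | SE unadjusted | SE adjusted | variance ratio | unadjusted N matching 80 adjusted (80/ratio) | power unadjusted | power adjusted |
|---|---|---|---|---|---|---|
| 0.3 | 0.265 | 0.213 | 0.65 | 123 | 47% | 65% |
| 0.5 | 0.224 | 0.194 | 0.75 | 107 | 61% | 73% |
| 0.7 | 0.173 | 0.160 | 0.85 | 94 | 82% | 88% |
| 0.8 | 0.141 | 0.134 | 0.90 | 89 | 94% | 96% |

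Standard errors are in baseline SD units. Generalised least squares on all three visits gives the same standard errors under compound-symmetric and first-order autoregressive correlation, so the 12-month visit does not remove the difference.

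**Check on the bounded score.** A simulation of the 0 to 8 score (40 per arm, 3,000 runs, independent domains, baseline tertile cut-points reused at follow-up, no effect) gave these standard deviations of the estimate in points, unadjusted then adjusted:
- domain correlation 0.3: 0.451 and 0.355
- 0.5: 0.404 and 0.337
- 0.7: 0.335 and 0.297
- 0.8: 0.289 and 0.265

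At 0.5 the variance ratio is (0.337/0.404)² = 0.70. This is below 0.75 because cutting into tertiles weakens the correlation of the composite. The gain therefore carries over to the actual scale.

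**Check on bias.** With no effect, mean estimates were 0.003 to 0.015 points unadjusted and 0.004 to 0.012 adjusted. With an effect of 0.3 SD per domain and domain correlation 0.5 they were 0.877 and 0.872. Neither method is biased, and both estimate the same quantity.

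**The case against.** **The article leaves the baseline handling open.** It names a mixed model with a group-by-time interaction. A model with a common baseline mean is also such a model, so the better form already fits the wording. An article may leave covariates to an analysis plan that is not shown. This stands to the extent that nothing in the text is wrong, and a reader should not infer that the plan commits itself to raw change scores or rules out adjustment. But the section does choose the model and the treatment term, and the form most analysts would fit from those words is the less precise one.

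**A reader might infer bias from regression to the mean.** The documents do not support that. Under 1:1 randomisation it acts on both arms alike, and the simulation shows no bias. A chance baseline imbalance does move the unadjusted estimate, but that movement is already in its standard error. For independent domains the composite SD is √(4 × 2/3) = 1.63, and a one-SE imbalance is 1.63 × √(2/40) = 0.36 points. At rho 0.5 it shifts the estimate by 0.5 × 0.36 = 0.18 points, half of the unadjusted SE of 0.36. This is the precision point again, not a second harm.

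**A reader might also infer that adjustment cures a ceiling.** It does not. The bound belongs to the 0 to 8 score, and both methods estimate the same difference on it. With independent domains about 1.3% of participants start at 8.

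**The gain may be small.** At rho 0.8 it is 10% of the variance. That is fair, and the range should be quoted rather than one value.

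**Adjustment is not free of conditions.** Equal expected baselines hold for everyone randomised. They need not hold in the subset with a measurement after baseline, and the delivery section treats retention as acceptable "with a dropout rate below 35% indicating acceptable retention". This stands and shapes the fix.

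**Conclusion.** The point holds as one of precision only. The stated model is valid and unbiased, but in its ordinary form it gives up 10% to 35% of the variance that baseline adjustment would save, for rho from 0.8 down to 0.3. At rho 0.5, 80 participants analysed with adjustment are worth about 107 analysed without it. These sizes rest on an assumed rho and on equal variances at the two visits; the power figures also rest on an assumed effect of 0.5 SD. If the sponsor already intends a common baseline mean or a baseline covariate, the gain is already there and only the wording needs to change. This is an inexpensive improvement worth making, not an error that threatens the trial's conclusions.

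**What to change.** Add one sentence to the Statistical analysis section saying that the models for the composite and for each domain adjust for baseline, in one of two ways:

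- The 6- and 12-month values are the outcomes, with group, visit, group by visit, and baseline score by visit as terms.
- All three visits are outcomes, with a common baseline mean for both arms: visit, group at 6 months, group at 12 months, no group term at baseline, and an unstructured covariance.

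If the second form is chosen, include all randomised participants with a baseline value, including those with no later measurement, and amend the definition of the analysis set for these models accordingly.

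The cost is wording only: no added participants, visits or measurements. It should be settled before recruitment opens, which the Trial status section places in 2026.

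### The modified ITT rule selects on attendance after randomisation and discards baseline values that the planned mixed model could use; its qualifying measurement is also undefined

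*Protocol article*

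**What the plan says.** The Statistical analysis section of the protocol article sets the analysis population as a "modified intention-to-treat population, defined as all randomised participants with at least one post-baseline measurement", and says that this is in line with the FINGER study. It does not say which measurement counts or at which visit. The preceding text of the same section states that differences "from baseline to 6 and 12 months will be analysed using linear mixed-effects models", with a group-by-time interaction.

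The Outcome assessments section fixes the outcome schedule: "Data will be collected at baseline, and at 6 and 12 months post-randomisation, for all participants". Table 1 shows the same three time points, and the first one after baseline is month 6, the primary endpoint.

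The structured programme has one further contact. Its vascular and metabolic component "includes a follow-up appointment with clinical staff at 3 months", at which "blood biomarkers (lipids, glucose), blood pressure, weight, BMI and hip and waist circumference—will be measured". The section on the self-guided arm gives the visits common to everyone: all participants "will meet with the study nurse at screening, baseline and 6 months post-randomisation for health assessments". No 3-month visit is described for controls.

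The delivery section sets a retention criterion for the intervention group, "with a dropout rate below 35% indicating acceptable retention", where retention means completing the 6-month programme.

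**The concern.** Whether a participant has a post-baseline measurement is decided after randomisation and may depend on the assigned arm. One arm is asked to attend a gym two to three times a week, train at home on a digital platform, see a dietician and return at 3 months. The other receives advice at baseline and is assessed at 6 and 12 months. The two arms may well lose different numbers and different kinds of people.

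Change from baseline is correlated with baseline. If those who leave start from a different level than those who stay, and this happens to a different extent in each arm, removing their baselines shifts the estimated mean change unequally. The exclusion is also unnecessary: a mixed model that treats the baseline score as one of the repeated responses can use a participant who has only that value.

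A second, smaller matter is wording. Because the qualifying measurement is undefined, the sentence does not expressly rule out the 3-month values, which only the intervention programme generates.

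**Working it through.** **The plan's own figures.** The target of 80 (40 per group) was set without a formal calculation, so there is nothing to reproduce. The one usable figure is the 35% dropout limit. 0.35 × 40 = 14, so a rate below 35% means at most 13 of 40 (13/40 = 32.5%). This is a ceiling for the intervention arm. It becomes 13 exclusions only if every programme dropout also misses both the 6- and 12-month assessments.

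**Simple arithmetic (inputs assumed).** Let the between-visit correlation be ρ, the dropout proportions p_I and p_C, and the amount by which dropouts start below those retained g (in SD units). In each arm the retained baseline mean exceeds the all-randomised mean by p × g, and expected change falls by (1 − ρ) per SD of baseline. Hence

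bias = −(1 − ρ) × (p_I − p_C) × g.

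With ρ = 0.5, p_I = 0.35 and p_C = 0.10:

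- g = 0.5: −0.5 × 0.25 × 0.5 = −0.0625 SD
- g = 1.0: −0.5 × 0.25 × 1.0 = −0.125 SD

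With logistic dropout on baseline calibrated to the same rates, the values were −0.063 and −0.123 SD.

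**Simulation (inputs assumed).** There was no true effect, 40 per arm, visits at 0, 6 and 12 months, correlation 0.5 and 1000 runs per scenario, with a generalised least squares form of the random-intercept model. The contrast is group by 6 months, in SD units, with Monte Carlo standard error 0.008–0.009. The last column lets a 3-month visit, attended by half of the intervention dropouts, count for entry.

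| Dropout | All randomised | mITT (6 or 12 months) | mITT, 3-month visit also counts |
|---|---|---|---|
| Random, 20% in each arm | 0.00 | 0.00 | 0.00 |
| About 36% vs 15%; low baseline more likely to leave, intervention arm only | 0.00 | −0.15 | −0.06 |
| Same, high baseline more likely to leave | 0.00 | +0.15 | +0.06 |
| About 36% in each arm, same baseline dependence | 0.00 | 0.00 | +0.09 |
| About 36% vs 15%; depends on unseen change, intervention arm only | +0.23 | +0.31 | +0.26 |

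The 36% is slightly above the protocol's limit. In the second row the standard error of the contrast was 0.261 under mITT and 0.252 with all randomised. The bias is therefore about 0.154/0.261 = 0.59 of a standard error, and keeping everyone cost no precision.

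**Can the 3-month visit supply an outcome value?** The composite needs diet, accelerometer, and cognitive and social activity data as well as vascular and metabolic measures. Only items from the last domain are listed at 3 months, so someone admitted through that visit alone would contribute just a baseline composite score.

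**The case against.** The population is prespecified, openly labelled as modified, and justified by consistency with the FINGER study. That source cannot be checked here. Disclosure and precedent explain the choice but do not remove the bias.

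The size depends on assumed dropout rates and mechanisms. This objection stands: the table shows no bias from the exclusion when dropout is random or follows the same mechanism in both arms. The 35% limit also concerns finishing the programme, not attending assessments. Someone who stops the programme but is assessed at month 6 or 12 stays in the set, as does someone who misses month 6 and attends month 12. Calling the set completers only would overstate it, and the limit should not be carried over to controls.

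A reader might also infer that the rule gives the intervention arm an extra route into the analysis through the 3-month visit. The documents do not support this. Outcome data are scheduled at the same three times in both arms, and the model sentence names only 6 and 12 months after baseline. The 3-month visit belongs to treatment delivery and is used for adherence: "Defined as attendance at the 3-month follow-up visit for cardiovascular assessments with clinical staff". It cannot yield the composite score. The natural reading gives both arms the same two opportunities to qualify. What remains is an undefined word. Counting the visit would not always do harm either: it moved the estimate towards the all-randomised result when dropout was higher in the intervention arm, and added 0.09 SD of bias when dropout was the same in both.

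**Conclusion.** The point holds as a low-cost improvement. The stated population selects on post-randomisation attendance and discards usable baseline values. If dropout differs by arm and depends on baseline, the 6-month contrast is biased by about 0.06 to 0.15 SD, in either direction according to who leaves. This range assumes about 35% loss in the intervention arm, 10–15% in control, a correlation of 0.5, and that those lost have neither a 6- nor a 12-month value. It is illustrative. It is not converted to points on the 0–8 score because the article gives no SD.

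Including everyone randomised removes this bias when dropout depends only on observed baseline. It does not rescue the estimate when dropout depends on unseen change, where +0.23 SD remained against +0.31 SD under the modified rule. The 3-month visit is an ambiguity to close, not a stated inequality between arms.

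**What to change.** In the Statistical analysis section:

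1. Define the primary analysis set as all randomised participants in their allocated arm, with every available composite score in the mixed model, including those from participants who have only a baseline value. The baseline score must be one of the repeated responses; a model of change scores alone could not use these participants.
2. Keep the modified ITT set as a sensitivity analysis.
3. Where that set is used, define the qualifying measurement as an outcome value at 6 or 12 months, and state that 3-month measurements do not determine inclusion.
4. State that the primary analysis relies on missing at random.

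The cost is a few sentences. The model, visits and data collection are unchanged, baseline is already scheduled for everyone, and the article's Trial status section places the start of recruitment in 2026.
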